### Data collection

The data for the CRF (Case Report Form) will be collected and recorded by the Clinical Research Assistant (CRA) from the patients’ medical files.

### Sample size

The sample size was defined using the appropriate formula for stepped wedge studies [30]. It was calculated by considering the most unfavorable situation that would result in a statistical difference, i.e 5% of pre- and post-operatively nutritional management in accordance with the current European guidelines in the control group vs. 20% in the intervention group. The significance threshold was fixed at 5%. The number of centers is 5 and the number of time period has been set at 6 to obtain optimum power. The coefficient of variation should be between 0.15 and 0.40, we set at 0.40 to be in the most pessimistic conditions. Five patients per center/step will be required for a power of 84%. This corresponds to a total of 150 patients (30 for each center).

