## Methods/design

### Study design

The ANC protocol is an interventional, comparative, prospective, multicenter, randomized protocol based on the stepped wedge trial design [30, 31], which is appropriate for allowing the implementation of a nutritional intervention in older patients by a Geriatric Team (GT) within all participating services. This design involves the sequential rollout of an intervention in centers over several time periods. The order in which the different centers will receive the intervention will be determined at random. The implementation of the intervention in the five participating centers will be rolled-out sequentially over six time periods (every six months), in such a way that each center will initially belong to the “control” arm (without GT intervention) and then to the “intervention” arm (with GT intervention) (Fig. 2). Depending on the center, the pre-intervention phase, as well as the intervention phase, will last from 6 to 30 months. Thus each center will also act as its own control, which will reduce risk of bias and will allow comparison between each support modality (interventional compared to control) and in each group to analyze the effect of time on the effectiveness of an intervention and its learning. The study design will also avoid contamination between patients.

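### The 84% power is reproduced only by giving the 20% arm the variance of the 5% arm; with the plan's own two rates, power is about 50%

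*Protocol article*

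**What the plan says.** The Sample size section of the protocol article relies on a stepped wedge formula taken from a cited source. Its inputs are:

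- **Effect:** "5% of pre- and post-operatively nutritional management in accordance with the current European guidelines in the control group vs. 20% in the intervention group", presented as the least favourable case.
- **Threshold:** "The significance threshold was fixed at 5" percent, with no statement of one- or two-sided.
- **Design:** "The number of centers is 5 and the number of time period has been set at 6 to obtain optimum power".
- **Between-center variation:** "The coefficient of variation should be between 0.15 and 0.40, we set at 0.40 to be in the most pessimistic conditions".
- **Result:** "Five patients per center/step will be required for a power of 84" percent, giving 150 patients, 30 per center.

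The section states neither the within-center variance nor the rate to which the coefficient of variation applies.

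Two other sections bear on the calculation. Study design fixes the switch pattern: "Depending on the center, the pre-intervention phase, as well as the intervention phase, will last from 6 to 30 months". With six-month periods, each center therefore has between one and five periods in each condition. Statistical analysis makes the primary comparison a mixed logistic regression that includes time.

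**The concern.** A binary outcome has a variance set by its rate: 0.0475 at 5% and 0.16 at 20%. A power calculation for these two rates has to let the larger variance enter for the intervention periods, which are half of the design. A simple benchmark suggests that it did not. An individually randomized comparison of 75 versus 75 patients, with no clustering and no period effects, has only 79.9% two-sided power for 5% versus 20%. A five-center stepped wedge that also pays for period adjustment and between-center variation should not exceed that.

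What is at stake is how the trial is read. Someone told that power was 84% would take a non-significant primary result as fair evidence against the intervention. If power was near 50%, such a result would be about as likely as not even if the planned effect were real.

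**Working it through.** **Inputs.** From Sample size: I = 5 centers, T = 6 periods, n = 5 patients per center-period, rates 0.05 and 0.20 (difference 0.15), coefficient of variation 0.40. From Study design: one center switches at each step, so there are 15 control and 15 intervention cells, or 75 patients in each condition. Assumed: a two-sided 5% test, and first a center SD τ = 0.40 × 0.05 = 0.02.

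**Formula** (Hussey–Hughes, center-period means, random center, fixed periods), with s² = within-center variance / n:

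Var = I·s²·(s² + T·τ²) / [(I·U − W)·s² + (U² + I·T·U − T·W − I·V)·τ²]

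- U, the number of intervention cells = 15.
- W, the sum of squared period totals = 0 + 1 + 4 + 9 + 16 + 25 = 55.
- V, the sum of squared center totals = 25 + 16 + 9 + 4 + 1 = 55.
- I·U − W = 75 − 55 = 20.
- U² + I·T·U − T·W − I·V = 225 + 450 − 330 − 275 = 70.
- Power = Φ(0.15/SE − 1.96).

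**Reproducing the stated figure.** Control variance in every cell: s² = 0.0475/5 = 0.0095 and τ² = 0.0004.

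Var = 5 × 0.0095 × 0.0119 / (0.19 + 0.028) = 0.002593, so SE = 0.0509, z = 2.946 and power = 83.8%. This matches the stated 84%.

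**Letting both rates enter the variance**, with τ = 0.02 and everything else unchanged:

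| Within-center variance | SE | Power |
|---|---|---|
| At the mean rate, 0.125 × 0.875 = 0.1094 | 0.0755 | 51.0% |
| Average of the two arms, (0.0475 + 0.16)/2 = 0.10375 | 0.0736 | 53.1% |
| Each arm's own variance (generalized least squares) | 0.0718 | 55.2% |

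For the averaged variance, s² = 0.02075 and Var = 5 × 0.02075 × 0.02315 / (0.415 + 0.028) = 0.005422.

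**Sensitivity to what the article does not state**, over these three variance choices:

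- Coefficient of variation of 0.40 applied to the mean rate (τ = 0.05): 46% to 50%. Applied to the 20% rate (τ = 0.08): 41% to 46%. Applied to each arm's own rate: 42% to 45%.
- No between-center variation at all: 53% to 57%.
- Linear instead of categorical time, arm-specific variances: 59% with τ = 0.02 and 61% with τ = 0.
- One-sided 5% test: at most 69% with categorical periods and 73% with linear time, both at τ = 0.

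**Effect at which the design does reach 84%** (two-sided, categorical periods, τ = 0.02): an intervention rate of 28% with arm-specific variances (84.1%), 29% with the averaged variance (84.1%), and about 31% with the variance at the mean rate (84.6%).

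**Patients needed for 84% at 5% versus 20%** (τ = 0.02): 11 to 12 per center-period, or 330 to 360 in total, against 5 and 150.

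The normal approximation is probably generous here, because a control cell expects only 5 × 0.05 = 0.25 events. A simulation of the planned logistic mixed model gave 51% by likelihood-ratio test (2,500 runs) and 38% by Wald test (600 runs). It was not independently repeated, and the conclusion does not rest on it.

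**The case against.** The variance actually used is inferred. The article names neither it, nor the base of the coefficient of variation, nor the sidedness, and the cited formula is not at hand. Nor is the route unique. Control variance with τ = 0.05 and a one-sided test also gives 84.4%. Some one-sided calculations without period effects land near 84% with both rates in the variance (84.2% with the variance at the mean rate and τ = 0.05). This stands as a limit on the diagnosis: the reliance on the control variance is established for calculations that include period effects. It does not rescue the figure. Dropping the period terms departs both from a stepped wedge formula with period effects and from the time-adjusted analysis that the article plans.

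The article's claim of pessimism, "we set at 0.40 to be in the most pessimistic conditions", concerns the coefficient of variation, where 0.40 is indeed the top of its stated range. It says nothing about the within-center variance. The fair criticism is only that this caution is outweighed by the smaller variance.

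Because 20% is offered as the least favourable effect, a larger true effect would fare better: at 5% versus 30% the same calculations give 83% to 89% with τ = 0.02. That is correct, but 84% is stated for 20%.

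Finally, the effect estimate and the type I error are untouched, and confidence intervals are already planned. This limits the harm, but it does not make the stated power true.

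**Conclusion.** The concern holds. On the article's own inputs, with period effects and a two-sided 5% test, power for 5% versus 20% is about 50%: 51% to 55% with τ = 0.02, and about 41% to 59% over the readings of the 0.40 coefficient of variation and of the time term. The stated 84% is too high by roughly 30 percentage points. The two assumptions the article leaves open, sidedness and the base of the coefficient of variation, do not change this. No combination examined exceeds about 73% once the 20% rate enters the variance and time stays in the model. That the control variance was used in both arms is the likely explanation, not a documented fact. As this is the power claim for the primary outcome, it must be corrected.

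**What to change.** Rewrite the Sample size paragraph to state that:

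- 150 patients give about 50% power for "in the control group vs. 20% in the intervention group" (control rate 5%), with a range of about 40% to 60% depending on the variance, the base of the coefficient of variation and the form of the time term;
- 84% power is reached only for about 5% versus 28% to 31%;
- the within-center variance used for each arm, the rate to which the 0.40 applies, and the sidedness of the test are as specified.

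Add that the primary result will be interpreted through its confidence interval in light of this power, so that a non-significant result is not taken as evidence of no effect.

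The cost is one reworded paragraph and a much less favourable stated power. Enrolment has begun, and no change in patient number, design or analysis is requested.

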### Statistical analysis

In order to ensure the objectivity of the results, the statistical analysis for this study will be performed by an independent statistician at the end of the follow-up period of the last patient included. The data will be analyzed using the SAS 9.1 software (Cary Inc., North Carolina, USA). No intermediate analysis is planned. Confidence intervals will be calculated according to an alpha risk of 5% and the statistical test results will be given a 5% threshold.

Univariate descriptive analysis will be used. The patients’ characteristics will be described and compared between the subsequent time points of the centers in which the intervention has started (intervention group) and those in which it has not (control group). The analysis will concern the patients’ demographic (age, sex) and clinical (antecedents and associated illnesses, surgical indication, etc.) characteristics, as well as the type and location of the intervention that has been performed. The comparisons will be evaluated using the Student *t*-test or the corresponding nonparametric test for the quantitative variables (average comparisons) and the Chi-Square or the Fisher’s test for the qualitative variables (percentage comparisons).

Concerning the primary endpoint analysis, the nutritional management of pre- and postoperative rate according with the recommendations will be compared before and after implementation of the intervention. This comparison will be performed by a logistic regression integrating time and the group (intervention / control) and an adjustment on the group (GLMM = generalized linear mixed model).

The support levels before and after implementation of the intervention will be presented on a gross basis and compared using a Chi square test. A graphical analysis will view the support levels before and after implementation of the intervention for each of the centers.

Concerning the analysis of secondary outcomes:

The percentage of subjects who underwent screening and the percentage of patients who received a care prescription will also be compared using a GLMM.

Globally (without taking into account the intervention) will be described:* malnourished subjects, malnourished subjects who could not get a prescription for nutritional management, severe malnourished patients, cachectic subjects among all subjects who underwent screening (percentage and 95% confidence interval)* the emotional score, the mini GDS on subjects who received screening, the number of concomitant treatments and specialties, the number of food intake on the number of prescribed taken, the average change in IADL score (mean, standard deviation, median, minimum, maximum).

The percentage of complications will also be compared between subjects who received nutritional support and those who don’t have benefited of this support by a Chi square test.

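### A crude before/after Chi-square test of the primary endpoint stands beside the time-adjusted GLMM without being labelled descriptive, and about 47% of any linear secular rise enters its contrast

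*Protocol article*

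**What the plan says.** The protocol article, Study design, describes an intervention "rolled-out sequentially over six time periods (every six months" in five centers. Each center starts in control, then moves to intervention, and each phase lasts 6 to 30 months depending on the center.

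Statistical analysis treats the primary endpoint (nutritional management that follows the recommendations) in two steps. First comes a model: "This comparison will be performed by a logistic regression integrating time and the group", with "an adjustment on the group (GLMM = generalized linear mixed model". The next paragraph adds: "The support levels before and after implementation of the intervention will be presented on a gross basis and compared using a Chi square test". It then announces a graph for each center. This paragraph stands before the secondary outcomes are introduced, so it concerns the primary endpoint.

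The same section says that "the statistical test results will be given a 5% threshold", with no exemption for the crude comparison. It does not say that the Chi-square is descriptive, or which result counts if the two differ.

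**The concern.** In a stepped wedge the order of switching is randomised, but being before or after the switch is tied to calendar time: control cells are early and intervention cells are late. A pooled before/after Chi-square has no period term, so a general improvement in practice during the 36 months of the study would appear partly as an intervention effect. The protocol itself foresees effects of time, in Study design and again in the Discussion.

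At stake is which p-value the trial report rests on. If practice drifts upward in all centers, the Chi-square can be significant when the intervention does nothing, and no rule in the article prevents it from being quoted when the model is not significant.

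**Working it through.** **Inputs.** From Sample size: "The number of centers is 5 and the number of time period has been set at 6 to obtain optimum power"; 5 patients per center and step; 150 patients; coefficient of variation (CV) 0.40; 5% conformity "in the control group vs. 20% in the intervention group"; 5% threshold, taken as two-sided because sidedness is not stated. From Study design: phases of 6 to 30 months, read as one center switching at each step. No secular trend is given anywhere, so the trends below are assumptions.

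**1. The plan's own power.** Stepped-wedge Wald formula (Hussey-Hughes), with I = 5 centers and T = 6 periods. For the layout above, U = 15, W = 55 and V = 55 (number of intervention cells, and sums of squared period totals and center totals). The cell variance is s² = 0.05 × 0.95 / 5 = 0.0095, and the center variance is τ² = (0.40 × 0.05)² = 0.0004.

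Var = I·s²·(s² + T·τ²) / [(I·U − W)·s² + (U² + I·T·U − T·W − I·V)·τ²]

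= 5 × 0.0095 × 0.0119 / (20 × 0.0095 + 70 × 0.0004)

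= 0.00056525 / 0.218 = 0.002593, so SE = 0.0509.

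Power = Φ(0.15 / 0.0509 − 1.96) = 83.8%, which matches the stated 84%. That power belongs to an analysis with period effects and a center effect, not to the Chi-square.

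**2. Calendar position of the two arms.** Control cells in periods 1 to 6 number 5, 4, 3, 2, 1, 0, so the mean period is 35/15 = 2.33. Intervention cells number 0, 1, 2, 3, 4, 5, so the mean period is 70/15 = 4.67. The gap is 2.33 periods × 6 months = 14 months. Each arm has 15 cells, or 75 patients.

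**3. Share of a trend that enters the crude difference.** A linear rise of total size D from period 1 to period 6 has slope D/5 per period. The crude difference it creates is (7/3) × D/5 = 7D/15 = 0.467·D.

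**4. Rejection by the crude test with no intervention effect.** The test is the Pearson Chi-square without continuity correction, 75 versus 75, two-sided 5%. Without center variation, each arm's number of conforming patients is a sum of binomials over its cells, and the rejection probability is exact. With CV 0.40 it was simulated (40,000 trials per scenario). The ranges cover separate simulation runs.

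| Assumed rise over six periods | Crude difference (7D/15) | Rejection, no center variation | Rejection, CV 0.40 |
|---|---|---|---|
| none (5%) | 0 points | 4.9% | 5.3-5.5% |
| 5% to 10% | 2.3 points | 8.7% | 9.0-9.6% |
| 5% to 15% | 4.7 points | 15.8% | 16.4-17.5% |
| 5% to 20% | 7.0 points | 25.2% | 25.9-27.2% |
| 5% to 30% | 11.7 points | 47.7% | 47.8-47.9% |

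The first row shows that clustering alone moves the error rate by about half a point. The growth down the columns comes from the missing period term.

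**5. The same data with period and center in the model.** A cell-level linear model with period and center effects, used as a stand-in for the GLMM, has an expected estimate of 0.0 points under every one of these trends. It rejects in 4.7% to 5.3% of simulated trials. With a rise from 5% to 20%, the Chi-square is significant while this adjusted model is not in 23-24% of trials with no effect.

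**The case against.** The strongest reply is that the plan already handles time. The comparison named first for the primary endpoint includes time, and the sample size uses a stepped-wedge formula. The Chi-square comes later, beside a graph, as part of a crude presentation, and unadjusted results are often reported next to adjusted ones. This stands as far as it goes: a reader might infer that the primary analysis ignores calendar time, and the article does not support that. It does not remove the point, because the crude comparison is a stated test at 5% with no label and no order of precedence.

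The trends are also assumed. The Background reports over 95% non-conformity in a pilot and says guidelines are rarely followed. A rise to 20% or 30% without intervention would match or exceed the planned intervention rate, so the larger figures are upper scenarios. A continuity correction would lower them to about 4%, 10%, 18% and 38% for the four rises, but the article names a plain Chi-square. These objections limit the size, not the direction, of the bias.

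A reader might also infer that the Chi-square would be the more powerful test and so the tempting one to quote. The documents do not establish that. On the plan's own figure the stepped-wedge analysis has 84% power, against 79.9% for a simple comparison of 75 with 75. The model is weaker only under other variance choices: its power is 51.0% with the variance at the mean rate of 12.5%, and 53.1% with the average of the two arm variances.

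**Conclusion.** The point holds for the crude test, and only for it. As written, the plan contains a second significance test of the primary endpoint that is biased whenever practice drifts over time, and it does not say that the GLMM decides.

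The size depends on a trend the documents do not give. Close to 5% of null trials reject with no rise, about 9% with a modest rise (5% to 10%), and 25-26% with a rise as large as the planned effect (5% to 20%). In that last case the spurious difference is 7 points, almost half of the planned 15. The calculation assumes a linear trend common to all centers, one center switching per step and full cells of five.

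Two stronger readings fail. Not all of a secular improvement is counted as effect; for a linear rise the share is 7/15. Treating clustered patients as independent is not a material source of error here, since rejection is about 5.5% at CV 0.40 with no trend.

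The model sentence has a related fault: it adjusts on the group, which is already a term in the model, and does not name center. The change is worth making, but the primary analysis does not fail because of this test.

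**What to change.** In Statistical analysis, remove the Chi-square comparison of support levels. Keep the crude percentages, by phase and by center and period, with the planned graph, as description without p-values.

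State that inference on the primary endpoint rests solely on the GLMM with period effects and a center effect, and replace the adjustment on group with adjustment on center.

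This changes two sentences and adds one. It needs no new data, patients or resources and leaves the sample size as it is. According to Trial status, data cleaning and analysis had not begun when the article was submitted; the change should be recorded before any outcome data are analysed.

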### ANC study schedule

In each surgical department involved in the study, the surgeon will screen all patients for trial eligibility during a preoperative surgical consultation. Patients in the observational period will receive the usual care, in accordance with the current practices of the unit. In the interventional period, the surgeon will inform the patient of a systematic preoperative geriatric assessment.

For the implementation of the intervention, the GT assessment will be standardized for all centers. It will last approximately 90 min and will be carried out by the GT team, together with a dietician, in the surgery or anesthesia unit, depending on the practices of the center. A nutritional management plan, adapted to the nutritional status of the patient, will be prescribed and implemented following this assessment, in accordance with the current recommendations and decision algorithm (Fig. 4).

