### Outcome and measurement

The primary outcome measure is to determine the impact of the geriatric intervention on the level of perioperative nutritional management, in accordance with the current European guidelines, of patients aged 70 years old or above who are undergoing surgery for colorectal cancer. This will be accomplished by evaluating the percentage of patients having received a nutritional screening i.e. measurement of body weight and size, calculation of the body mass index (BMI), evaluation of a recent body weight loss and an albumin assay at least 7 days before surgery, and having received oral immunonutrition during 7 days before surgery (if absence of malnutrition) or immunonutrition during 7 days before and 7 days after surgery (if moderate malnutrition) or artificial nutrition during 7–14 days before surgery and 7 days after surgery.

The secondary outcomes are:The percentage of patients having received a nutritional screening, i.e. measurement of body weight and size, calculation of the body mass index (BMI), evaluation of a recent body weight loss and an albumin assay at least 7 days before surgery.The percentage of patients having received oral immuno-nutritionThe percentage of patients with undernutrition, severe undernutrition and cachexiaThe rate and type of postoperative complications, from grade I to V, according to the Common Terminology Criteria for Adverse Events v4.0 (CTCAE) of National Cancer Institute, occurring up to 30 days after surgery.The number of actual oral nutritional supplements intakes with respect to planned ones (noted in the patient diary given at the preoperative geriatric assessment).The comparison of functionality scores obtained on the ADL and IADL, evaluated by the GT between the beginning (between 14 and 7 days before surgery) versus the end (after surgery, the day before or the day of discharge from the surgical ward) of the hospitalization period.The emotional state of the patient evaluated with the mini-GDS (score on 4) and the GDS 15 (if mini GDS score >2).The number of concomitant treatments (number of drug specialties between 0 and 3, between 3 and 6, over 6) during the hospitalization period.

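### The listed secondary outcome is oral immunonutrition received, but the planned GLMM compares care prescribed, which is partly a measure of intervention delivery

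*Protocol article*

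**What the plan says.** Under Outcome and measurement, the protocol article lists as separate secondary outcomes the percentage of patients screened and the percentage who received oral immunonutrition. A further item is "The number of actual oral nutritional supplements intakes with respect to planned ones", recorded in a diary that the patient gets at the preoperative geriatric assessment.

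Under Statistical analysis, only two secondary variables go into the mixed model. One is the percentage screened. For the other, "the percentage of patients who received a care prescription will also be compared using a GLMM". Intake appears only in a descriptive list, as "the number of food intake on the number of prescribed taken", and that list opens with "Globally (without taking into account the intervention) will be described".

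Under ANC study schedule, prescribing belongs to the intervention period: a nutritional plan "will be prescribed and implemented following this assessment, in accordance with the current recommendations and decision algorithm". For the control period, "Patients in the observational period will receive the usual care, in accordance with the current practices of the unit".

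**The concern.** The variable to be tested is not the outcome that was listed. It differs in two ways: prescribed instead of received, and any nutritional care instead of oral immunonutrition. Because the geriatric team's assessment is meant to lead to a prescription, comparing prescription rates between phases largely asks whether the team did its part. It says less about whether patients took the nutrition.

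A secondary analysis of receipt would help to show whether a change in the primary composite came from screening or from feeding. The prescription contrast cannot show that, yet it could be reported as support for the primary result.

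**Working it through.** The plan states no figure for this point. Its planning rates (5% versus 20%, power 84%) belong to the primary composite and do not bear on it. The check is therefore a comparison of sections, followed by algebra with assumed rates.

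**1. Listed outcome against planned analysis**

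- Screening: listed, and compared by GLMM. These match.
- Oral immunonutrition received: listed, but the GLMM is on care prescription. These do not match.
- Actual against planned intakes: listed, but only described, pooled over phases. This cannot correct a between-phase contrast.
- The crude Chi-square comparison and the per-center graph follow the primary endpoint in the text and appear to concern that composite. They do not supply the missing analysis.

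**2. Is prescription just another word for receipt here?**

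The descriptive list sets intake against what was prescribed. It also has a separate item for malnourished subjects who got no prescription. Prescription is thus its own variable in this plan.

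**3. Direction of the difference**

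Let pI and pC be the prescription rates in the intervention and control phases, and aI and aC the uptake among those prescribed. Assume that receipt requires a prescription, so received = p × a.

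- Risk difference (RD), prescribed: pI − pC
- Risk difference, received: pI·aI − pC·aC
- Prescribed minus received: pI(1 − aI) − pC(1 − aC)

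With equal uptake below 100% and pI > pC, the last line is always positive. In general it turns negative once aI exceeds 1 − pC(1 − aC)/pI.

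**4. Illustration (all rates assumed)**

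For the first row: received = 0.60 × 0.70 = 0.42 and 0.05 × 0.70 = 0.035. The risk difference is 0.42 − 0.035 = 0.385, and the odds ratio (OR) is (0.42/0.58)/(0.035/0.965) = 20.0.

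| pC | pI | aC | aI | RD prescribed | RD received | OR prescribed | OR received |
|---|---|---|---|---|---|---|---|
| 5% | 60% | 70% | 70% | 0.55 | 0.385 | 28.5 | 20.0 |
| 5% | 90% | 70% | 70% | 0.85 | 0.595 | 171.0 | 46.9 |
| 5% | 60% | 50% | 90% | 0.55 | 0.515 | 28.5 | 45.8 |
| 20% | 60% | 50% | 90% | 0.40 | 0.44 | 6.0 | 10.6 |

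The third row reverses on the odds-ratio scale only. The fourth reverses on both scales.

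**5. Break-even intervention uptake on the risk-difference scale**

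- pC 5%, pI 60%, aC 50%: 1 − 0.025/0.60 = 0.958
- pC 5%, pI 90%, aC 70%: 1 − 0.015/0.90 = 0.983
- pC 30%, pI 60%, aC 50%: 1 − 0.15/0.60 = 0.75

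Where control prescribing is rare, overstatement fails only at nearly complete intervention uptake. Where control prescribing is common and control uptake is poor, it fails much sooner.

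**The case against.** The strongest reply is that receipt is already compared between phases. The primary composite requires nutrition actually received for set durations and is analysed by GLMM, so a good prescription rate could not hide a failure to feed patients. This stands, and it limits the point to one secondary analysis. What is missing is a separate test of the immunonutrition component.

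A second reply is that this is a condensed article and the phrase may be a loose rendering of care received. That cannot be excluded. But the article names both the variable and the model, and elsewhere it keeps prescribed and taken apart, so a statistician following it would analyse a different variable. Prescribing is also a legitimate process measure in an implementation trial, which is a reason to report it but not to substitute it.

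Stronger readings are tempting. A reader might infer that every intervention-phase assessment ends in a prescription, so that the contrast is close to guaranteed. The schedule section states that intention. However, the analysis section expects some malnourished subjects without a prescription, and the ANC program section has the team proposing management and offering the assessment at the surgical unit's request. A reader might also put a figure on the overstatement: full prescribing with 60% to 90% uptake gives a gap of 10 to 40 points in the intervention phase. That only restates the assumed uptake. Nor is overstatement certain, since the model is a logistic one and the odds ratio can move the other way.

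**Conclusion.** The mismatch between the listed outcome and the analysed variable is in the text and should be corrected. The prescription contrast partly measures delivery of the intervention. It is likely to overstate the effect on nutrition received, provided uptake is incomplete and not much worse in the control phase. The documents support neither a size nor a certain direction. The primary endpoint, sample size and power are not affected.

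**What to change.** In the Statistical analysis section, apply the GLMM to the percentage of patients who received oral immunonutrition, with the same definition in both phases. Report the prescription rate separately, labelled as a process measure of intervention delivery.

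Name one source for receipt that exists in both phases. The intake diary will not serve, because it is handed out at the geriatric assessment, which is not systematic in the control period. The patients' medical files, named under Data collection as the source for the case report form, are the obvious candidate.

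The cost is about one sentence on the analysis and a clause on the source. Receipt in both phases is already needed for the primary endpoint, so no new data item is required. Trial status says that data cleaning and analysis had not begun at submission.
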